## 6.6 Blinding

It is a single-blinded controlled clinical trial. Investigators, including ophthalmologists and optometrists, who are responsible for collection of data related to myopia progression will be blinded to study intervention. Masking subjects and their parents or guardians is not feasible since the lens design of the DIMS lenses and single vision lenses is easy to be detected. A data monitoring committee will be established to review adverse events during the study and ensure the safety of the study participants. He or she is also responsible for allocation of participants to different study groups. The masking procedures fulfil the CONSORT requirements for a single masked randomized clinical trial. The participants will be asked to wear the spectacles in full-time mode. A log sheet or an access to an online platform will be given to the participants, their parents or guardians for recording usage of eye drops. Compliance will be monitored and checked by phone calls and questionnaire.

## 6.7 Withdrawal Criteria

Participants (or parents / guardians for participants <18 years of age) are free to withdraw from participation in the study at any time upon request. No further data will be collected on participants who withdraw themselves from this study. If significant intolerance to study treatment is suspected at any time after randomization, participants may be requested to withdraw from the study at any time.

An investigator may discontinue or withdraw a participant from the study due to the following reasons:

- Significant study intervention noncompliance: unable to contact via three phone calls, more than three attempts to arrange missed follow-up appointments, wearing the spectacles less than five days a week and / or weekly average less than five hours/day.
- If any clinical adverse event or situation occurs (e.g. allergies to eye drops, reduction of visual function such as diplopia, reduction of BCVA; subject to clinicians’ judgement) such that continued participation in the study would not be in the best interest of the participant.
- If the participant meets an exclusion criterion (either newly developed or not previously recognized) that precludes further study participation.

Should participants require discontinuation of study treatment for any reason, or if they select to cease taking treatment, follow-up visits and data collection will not be continued as scheduled. The reason of discontinuation or withdrawal of participant from the study will be recorded on the Discontinuation / Withdrawal Case Report Form (CRF W) in Research Electronic Data Capture (REDCap). The use of REDCap can help reduce human errors in the randomization process, to assist data collection, and to provide a real-time dashboard for monitoring the project progress. Participants who sign the informed consent form, and are randomized but do not receive the study intervention may be replaced. If there are participants who signed the informed consent form, are randomized and received the study interventions but discontinue or withdraw within the first two weeks due to inability to meet inclusion criteria (e.g. unable to tolerate spectacles or eyedrops), and it is still within the recruitment period, then randomization of these participants will be discarded and replaced with a participant from the next allocation. All spectacles and eye drop (used or unused) will be returned to the investigator on withdrawal or discontinuation from the study.

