## 6.14 Protocol Violations

A deviation from the protocol when no amendment has been submitted and approved would be regarded as a protocol violation. All protocol violations must be documented and reported (CRF V in REDCap). Prescribed treatment dose of spectacles is at least 70 hours each week (10 hours of spectacle wear per day, 7 days a week) and treatment dose of eye drop is two drops of eye drop every day, seven days a week. A participant is considered as compliant to the study protocol if he or she has worn the spectacle for at least 56 hours a week (7 days of at least 8 hours). If the spectacle lenses are worn for less than 35 hours per week, or eye drops are put on for less than three days per week, it is defined as a protocol violation. A list of such patients will be prepared prior to unblinding.

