### 7.2.4 Procedures to account for missing data

All analyses will use intention-to-treat analyses. Missing values of outcome variables and covariates will be replaced using multiple imputation procedure with 10 sets of imputations assuming missing at random. Sensitivity analyses for the primary outcomes include: complete case analysis and per-protocol analysis.

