Information to be collected includes event description, time of onset, clinician’s assessment of severity, relationship to study product (assessed only by those with the training and authority to make a diagnosis), and time of resolution or stabilization of the event. All AEs occurring while on study must be documented appropriately regardless of relationship. All AEs will be followed to adequate resolution. An appointment will be arranged for four to six weeks following AE resolution to check for any recurrence or changes as a result of the AE. Changes in the severity of an AE will be documented to allow an assessment of the duration of the event at each level of severity to be performed. AEs characterized as intermittent require documentation of onset and duration of each episode. These will be followed-up and assessed by medically fit clinician. It will be left to the judgement of the Steering Group to decide whether or not an AE is of sufficient severity to require discontinuing the participant from the study. A participant may also voluntarily withdraw from participating in the study due to what he or she perceives as an intolerable AE. If either of these occurs, the participant must undergo follow-up visits for trial assessment and be given appropriate care under medical supervision until symptoms cease, or the condition becomes stable.

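### Outcome measurement stops when treatment stops, so the intention-to-treat analysis depends on imputation from children still on treatment

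*Combined protocol and SAP*

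**What the plan says.** Section 6.7 has four relevant rules.

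- After self-withdrawal: "No further data will be collected on participants who withdraw themselves from this study".
- After treatment stops for any reason, including the child's own choice to stop: "if they select to cease taking treatment, follow-up visits and data collection will not be continued as scheduled". No alternative schedule is given.
- "An investigator may discontinue or withdraw a participant from the study due to the following reasons". One listed reason is non-compliance, which includes "wearing the spectacles less than five days a week and / or weekly average less than five hours/day".
- If a child has received the intervention but leaves within two weeks, for example because the spectacles or drops are not tolerated, and recruitment is still open, the "randomization of these participants will be discarded and replaced with a participant from the next allocation".

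Section 7.2.3 adds that treatment is discontinued for treatment-related adverse events.

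On analysis, Section 7.2.4 states: "All analyses will use intention-to-treat analyses". Missing outcomes and covariates are filled by 10 imputations under missing at random, and the sensitivity analyses are complete-case and per-protocol. The statistical methods in Section 1 say the same.

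Section 9.1.2 covers a child who is discontinued from the study, or who withdraws, because of an adverse event. It says that "the participant must undergo follow-up visits for trial assessment".

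**The concern.** Both primary outcomes are changes from baseline to 18 months (Section 6.10). An intention-to-treat comparison needs that value for all randomised children, including those who stopped. Section 6.7 treats stopping treatment as leaving the study, so these values are lost by design.

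Missing-at-random imputation can only learn from observed data, and here those come almost wholly from children still on treatment. A child who stopped at month 9 is given the 18-month value expected of a child in the same arm who carried on. If children who stop then progress faster, the reported effect lies closer to the effect of continued treatment than to the effect of assigning it. Families are unmasked and the lenses can be told apart (Section 6.6), so stopping could also differ between arms.

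Discarding early leavers is a more direct departure from intention-to-treat, because randomised children are removed for a reason arising after allocation.

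**Working it through.** **1. The plan's own figure.** Section 7.1 assumes an AT change of 0.64 D, SD 0.56 D, and a 60% reduction: 0.64 x 0.60 = 0.384 D, so the ATD change is 0.64 - 0.384 = 0.256 D. A two-sample t-test with two-sided 5% significance and 90% power needs 45.7 per group, rounded to 46 (power 0.902). The plan's 46 reproduces. With 56 per arm and 20% lost, 56 x 0.8 = 44.8 are measured, and power is 0.889 at 44 and 0.896 at 45. Lost precision is therefore minor. The issue is what is estimated.

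**2. Assumptions for children who stop.** The documents give no off-treatment rate. Section 4.2.1 credits 0.01% atropine with a 20% reduction, so I take 0.64 / 0.8 = 0.80 D per year. Shares and times of stopping are also assumed. Only the 20% has a source: it is the total dropout rate in Section 7.1.

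**3. Formula.** For share d stopping at month t of 18:

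arm mean = on-treatment mean + d x (1 - t/18) x (0.80 - on-treatment mean)

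Example, 20% in each arm at month 9: AT = 0.64 + 0.2 x 0.5 x 0.16 = 0.656; ATD = 0.256 + 0.2 x 0.5 x 0.544 = 0.310; difference = 0.346 D; 0.384 / 0.346 = 1.11.

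| Stopping AT / ATD | Month | All-randomised difference (D) | 0.384 D too large by | Power, all 56 per arm measured |
|---|---|---|---|---|
| 20% / 20% | 0 | 0.307 | 25% | 82% |
| 20% / 20% | 6 | 0.333 | 15% | 88% |
| 20% / 20% | 9 | 0.346 | 11% | 90% |
| 20% / 20% | 12 | 0.358 | 7% | 92% |
| 10% / 10% | 0 | 0.346 | 11% | 90% |
| 10% / 10% | 9 | 0.365 | 5% | 93% |
| 10% / 30% | 0 | 0.237 | 62% | 60% |
| 10% / 30% | 12 | 0.335 | 15% | 88% |
| 30% / 10% | 0 | 0.378 | 1.7% | 94% |
| 30% / 10% | 12 | 0.382 | 0.6% | 95% |

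With equal stopping the formula reduces to 0.384 x (1 - d x (1 - t/18)). The off-treatment rate cancels, so those rows do not depend on 0.80 D so long as it is the same in both arms. Power keeps the SD at 0.56 D. The inputs are 12-month figures; the ratios carry to 18 months if progression is linear.

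**4. What the planned imputation returns.** I simulated 1,500 trials with 56 per arm, 20% stopping at random, and 10 imputations using arm and the 6-month value.

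| Stop at | Planned imputation | Complete-case | Had stoppers been measured |
|---|---|---|---|
| Month 9 | 0.381 D | 0.382 D | 0.344 D |
| Month 6 | 0.387 D | 0.387 D | 0.336 D |

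Imputation and complete-case agree with each other, and both miss the all-randomised value. Their agreement would look reassuring and would not be.

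**5. The two follow-up rules.** Section 6.7 ends scheduled visits after a stop for any reason. Section 9.1.2 requires trial-assessment visits after an adverse-event discontinuation or withdrawal. A child stopped under Section 7.2.3 could be handled under either.

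**The case against.** A reader might infer that intention-to-treat cannot be done. That goes too far. The plan specifies imputation of missing outcomes, so an analysis of the children kept in the randomised set can be run. It rests on an untestable assumption and targets something close to the on-treatment effect.

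A reader might also infer that the result is biased as a matter of fact. The size depends on how many stop, when, in which arm and how they then progress. It is near zero if stopping is rare or mostly in AT. Nor do the documents show an arm shedding poor responders: the withdrawal reasons in Section 6.7 are non-compliance, adverse events and eligibility.

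Withdrawal for low wear is discretionary, so some poor adherers will stay and be measured. Section 9.1.2 may already secure outcomes after adverse-event stops, although it ties follow-up to the event settling and could mean safety visits only. The negative in the Section 6.7 sentence may even be a slip. Each of these points supports clarifying the text.

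The adherence cut-offs invite three further inferences that I would not draw.

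- The withdrawal and violation limits are not the same. Five hours on seven days is 35 h/week, but Section 6.7 also has a days-per-week limb: four days at 10 hours is 40 h, which can lead to withdrawal but is not low wear under Section 6.14 ("worn for less than 35 hours per week, or eye drops are put on for less than three days per week").
- It does not follow that the per-protocol set collapses onto the complete cases. Section 6.14 plans a list of violators before unblinding, so some are expected to remain.
- That 3 of 14 weekly doses is acceptable is an extreme reading. Three days at the stated frequency is 6 of 14, and Section 6.14 opens by treating any unapproved deviation as a violation.

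**Conclusion.** The point holds in a limited form. Followed as written, Section 6.7 leaves few or no off-treatment 18-month outcomes, and the analysis labelled intention-to-treat would estimate roughly the on-treatment effect. Neither planned sensitivity analysis would reveal this. Discarding some early leavers departs from intention-to-treat directly. Sections 6.7 and 9.1.2 conflict and must be reconciled.

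With 20% stopping in each arm between the start and half-way, the overstatement is 11% to 25%. Across the patterns tried it runs from about 1% (stopping mostly in AT) to 62% (30% in ATD and 10% in AT, at the start). These figures rest on assumed stopping shares and times and, where arms differ, on the assumed 0.80 D per year. Section 7.1 does not split its 20%. Children who withdraw consent or cannot be reached would stay missing after any change, so not all of the gap is recoverable.

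I rate this as a cheap improvement. It is best made early, because an outcome never measured cannot be restored by later analysis wording. Section 2 lists the trial as not yet recruiting.

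**What to change.** 1. In Section 6.7, separate stopping treatment from leaving the study. Measure cycloplegic autorefraction and axial length at the scheduled 6-, 12- and 18-month visits in every randomised child unless consent to follow-up is withdrawn. Do not end outcome measurement for non-compliance.
2. Reconcile Sections 6.7 and 9.1.2 on follow-up after an adverse event, stating which visits are for outcomes and which for safety.
3. Keep all randomised children in the intention-to-treat set, including early leavers whose randomisation is now discarded.
4. In Section 7.2.4, add a missing-not-at-random sensitivity analysis beside the complete-case and per-protocol analyses, for example delta-adjusted or reference-based. State the off-treatment assumption: giving ATD leavers the AT trajectory supposes that they continue atropine.

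Clinical decisions to stop treatment are unchanged. Section 6.8 needs no edit for this purpose, since it already requires contact and rescheduling.

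The cost is protocol and consent wording, and some already-scheduled visits kept for children who stop. The target difference may also be smaller. With 20% stopping in each arm and all 56 per arm measured, power is about 82% to 92%, and 90% power would need 53 to 71 measured per arm depending on when children stop.

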# 7. Statistical Considerations

## 7.1 Sample Size

In the study regarding low dose atropine for myopia control, mean change in refractive error after one year was 0.64 ± 0.56D (mean ± SD) (10). Our previous randomized clinical trial showed DIMS slowed down myopia progression by approximately 60% (8). The sample size is calculated based on an assumption that, adopting atropine and DIMS together will result in a 60% reduction of mean refractive error change relative to using only atropine, the difference detected between two groups (atropine alone vs. atropine and DIMS) will be 0.384 (0.64 x 60% = 0.384), and the effect size will be 0.685 (0.384/0.56 = 0.685). According to power analysis (G*Power Version 3.1.9.2), 46 subjects are required per group to achieve 90% power with a significance level of 0.05 (two-tailed). Assuming the dropout rate will be 20%, 56 subjects will be required for each group in this proposal. Therefore, 112 subjects (56 subjects × 2 groups) will be required for the entire study.

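### Section 6.7 voids the randomisation of children who stop within two weeks for intolerance, which contradicts the planned intention-to-treat analysis

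*Combined protocol and SAP*

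**What the plan says.** Section 6.7 (Withdrawal Criteria) has two replacement rules.

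- *Treated, then stopped within two weeks.* The stated reason is failure to meet inclusion criteria, with intolerance of spectacles or drops as the example. If recruitment is still open, "then randomization of these participants will be discarded and replaced with a participant from the next allocation".
- *Randomised, never treated.* "Participants who sign the informed consent form, and are randomized but do not receive the study intervention may be replaced". This rule is optional and says nothing about voiding the allocation.

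Section 6.7 also says that scheduled visits and data collection end once study treatment is discontinued, and that the reason goes on a withdrawal form. Section 9.1.2, by contrast, requires follow-up visits for trial assessment when a child leaves because of an adverse event.

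On analysis, Section 7.2.4 states: "All analyses will use intention-to-treat analyses". The Statistical Methods part of Section 1 says the same. Section 7.2.1 describes baseline for everyone randomised, and Section 7.2.3 summarises premature discontinuations by group and reason.

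On masking, Section 6.6 says "Masking subjects and their parents or guardians is not feasible", while those who collect progression data are masked. Section 6.5 gives the allocation sequence to an unmasked site coordinator.

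**The concern.** Intention-to-treat means that every randomised child is analysed in the assigned arm. A rule that voids some allocations after treatment has begun makes the analysed groups differ from the randomised groups.

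Removing a child found ineligible on facts fixed before randomisation can be defended. Tolerance of the assigned lens is not such a fact. Both arms receive the same drops, so the assigned treatments differ only in the lens. That makes lens intolerance the route by which removals could differ between arms. Families know which lens the child wears, and no masked or independent person is named to decide who falls under the rule.

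At stake are the membership of the primary analysis set and whether early failure to tolerate DIMS counts in the comparison that is meant to show whether adding DIMS helps.

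**Working it through.** **1. The plan's own figures (Section 7.1).** Control change is 0.64 D with SD 0.56 D. The target difference is 0.64 × 0.60 = 0.384 D, and the effect size is 0.384/0.56 = 0.686 (given as 0.685). A two-sample t-test at two-sided 0.05 and 90% power needs 45.77 per arm, so 46, which matches. The plan then says "Assuming the dropout rate will be 20%, 56 subjects will be required for each group in this proposal". This reproduces as 46 × 1.2 = 55.2, rounded up to 56. Dividing by 0.8 would give 57.5, so 58, but the present point does not depend on that. With 20% loss, 56 × 0.8 = 44.8, or about 45 per arm, remain.

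**2. When tolerance becomes visible.** Section 6.13.2 has the lens ordered according to randomisation. The schedule in Section 6.12 puts first dispensing at Visit 2, after randomisation at Visit 0-1. No trial wear of either lens before randomisation is described. Tolerance of the assigned lens is therefore a post-allocation observation.

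**3. Do the sections fit together?** A voided allocation (6.7) and an analysis of everyone randomised (7.2.4) cannot both hold for the same child. No section says that voided children remain in the analysis set. Multiple imputation fills gaps for children in the data set and cannot restore one who was taken out.

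**4. Possible bias.** Assumptions: a share f of one arm is removed, none of the other, and the removed children would have progressed g dioptres differently from the rest of their arm. The arm mean then shifts by f × g. With 56 per arm, the standard error of the difference is 0.56 × √(2/56) = 0.106 D. Type I error comes from the noncentral t distribution with 110 degrees of freedom and noncentrality f × g/0.106. The g values are 0.25, 0.5 and 1 SD. Cells show bias in D, then type I error.

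| f (children of 56) | g = 0.14 D | g = 0.28 D | g = 0.56 D |
|---|---|---|---|
| 2% (1.1) | 0.003; 0.0501 | 0.006; 0.0503 | 0.011; 0.0513 |
| 5% (2.8) | 0.007; 0.0505 | 0.014; 0.0520 | 0.028; 0.0579 |
| 10% (5.6) | 0.014; 0.0520 | 0.028; 0.0579 | 0.056; 0.0821 |
| 15% (8.4) | 0.021; 0.0544 | 0.042; 0.0679 | 0.084; 0.1234 |

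Against the target, 0.0028/0.384 = 0.7% and 0.084/0.384 = 22%. At 45 per arm the worst cell gives 0.108. Similar removals in both arms would partly cancel.

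**5. Price of keeping the children.** If a share f of ATD stops early, is still measured and gets no added benefit, the expected difference is 0.384 × (1 − f).

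| f | Difference (D) | Power, 45 per arm | Power, 56 per arm |
|---|---|---|---|
| 0% | 0.384 | 89.6% | 94.9% |
| 2% | 0.376 | 88.4% | 94.1% |
| 5% | 0.365 | 86.4% | 92.7% |
| 10% | 0.346 | 82.5% | 89.9% |
| 15% | 0.326 | 78.1% | 86.4% |

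**The case against.** The best defence is that Section 1 lists the ability to wear the prescribed spectacles among the inclusion criteria, so the rule only removes children who should not have entered. That fails for the reason in step 2: the criterion, applied to the assigned lens, cannot be checked before allocation.

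Other parts of the defence stand. The two-week rule runs only while recruitment is open. Drop intolerance, one of its two examples, is not expected to differ by arm on pharmacological grounds. Outcome assessors are masked. The bias is negligible if few children are removed or if they resemble the rest. Keeping the children is also not a complete cure: without 18-month data they would be imputed as missing at random, largely from children still followed, and much of any bias could remain.

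A reader might infer more than the documents support:

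- *Never-starters are deleted too.* The text says only that they may be replaced. Whether they stay in the analysis set is not stated.
- *Families learn their lens and leave before dispensing.* No section says the arm is disclosed before Visit 2.
- *The trial is unmasked.* Families and the coordinator are unmasked; assessors are not.
- *Early intolerance vanishes from the tolerability results.* Section 7.2.3 counts discontinuations for any reason by group. What is unclear is whether a child with a voided allocation is counted in a group.
- *Broken blocks bias the result.* Slight imbalance in numbers does not bias a t-test.

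**Conclusion.** The concern holds for the two-week rule. As written, it contradicts the intention-to-treat commitment whatever the number of children affected, because it decides who is in the primary analysis from an event after allocation that may depend on the arm. For never-starters the plan is ambiguous rather than wrong.

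The size and direction of any bias cannot be determined from the documents. The range of 0.003 to 0.084 D, with type I error of 0.050 to 0.123, rests on assumed removal of 2% to 15% from one arm only and an assumed gap of 0.14 to 0.56 D. The upper end needs both a high removal rate and a gap of a full SD, and nothing in the documents shows that early intolerance predicts progression that strongly. A middle case (10% removed, 0.28 D gap) gives 0.028 D and 0.058. The case for change rests on the contradiction, not on any one cell of the table.

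**What to change.** - Delete the rule that discards randomisation.
- Define the intention-to-treat set as all randomised children by assigned arm, including never-starters and early stoppers.
- If more children are recruited, randomise them as additions, with no earlier allocation voided.
- State that early stoppers are counted in their assigned arm in the Section 7.2.3 summary.
- Reconcile Section 6.7 (data collection not continued after discontinuation) with Section 9.1.2 (follow-up visits for trial assessment). It should be clear whether 18-month outcomes are sought for these children or whether they fall to the missing-data plan.

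Most of this is wording. If outcomes are to be sought, some visits are added. Early stoppers without outcomes use up the dropout allowance, which is 56 − 46 = 10 children per arm. If they are measured and gain no benefit from DIMS, power at 45 per arm falls by 1.2 to 11.5 points over the assumed 2% to 15% range. The stated power therefore becomes less favourable, slightly so if early stopping is rare.
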